## Sample Size

This study primarily aims to determine if routine intermittent treatment with antimalarials results in a reduction in childhood clinical malaria, by assessing time to first episode of clinical malaria.

We estimate that the median time to first episode of clinical malaria in the placebo group receiving iron is 18 months (68 weeks after the first intervention visit). The sample size required for 90% power to detect a protective efficacy of 40%, assuming =0.017, is 250 per arm. Alpha has been adjusted to 0.017 in order to account for multiple comparisons (3 arms each compared to the placebo group, Bonferroni adjustment 0.05/3 tests=0.017). Therefore, the study would require a total sample of 1000 infants (250 in each of 4 groups). We expect that 11% of infants will have the outcome measure at baseline and thus will be excluded from the primary analysis. Including this decrease and adjusting for a 10% loss to follow up and 13% mortality, the study will require 1516 infants (379 in each arm).

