## Assignment to interventions

All infants whose parents or guardians agree to participate in the study will be assigned to one of the 4 treatment groups through permuted block randomization[50]. The randomization code will be prepared before the trial starts.

These randomization procedures are expected to minimize the possible influence of geographical location and seasonal malaria variations.

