## Children who are febrile and parasitemic at enrollment

Infants who have documented fever (> 37.5 C by axillary measurement) or history of recent fever (in the previous 48 hours) will have a rapid diagnostic test (RDT) for malaria performed. If the RDT is positive, the infant will be given antimalarial treatment in accordance with national policy. A blood film will also be performed; febrile infants who had a negative RDT, but on later blood film examination have parasitemia will be given antimalarial treatment in accordance with national policy. These results and the antimalarial therapy will be delivered to the infant’s home only if the results of the blood film are positive while the RDT was negative. These patients will be included in the study.

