# Definitions

# A clinical malaria episode in an infant will be defined as an axillary temperature of at least 37.5C in combination with asexual *P. falciparum* parasitemia of any density . Mild-to-moderate anemia will be defined as Hb <11.0 and 8. Severe anemia will be defined as Hb <8 and 5. Critical anemia will be defined as Hb <5.

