**Data Management**

Data cleaning and storage:

Quantitative data will be entered using scan-ready forms and an optical scanner. Data will be entered and edited in Kenya. Images of scan forms will be kept on a secure server with access limited to study personnel. Data analysis will be undertaken collaboratively in Kenya and at CDC in Atlanta. Access to study computers will be restricted to study personnel, and paper records will be secured in locked cabinets in Kenya. Paper records will not be transported to Atlanta. Electronic files will be transferred to Atlanta either as password-protected e-mail attachments or as password protected files on zip disks or CDs.

Sample storage

Specimens will be stored in locked freezers or cabinets with identifiers at KEMRI and at CDC, to which only study personnel will have access.

In accordance with WHO advice, testing for serological responses to EPI antigens will be performed at a single commercial reference laboratory. The commercial laboratory will only have coded specimens, and will not be engaged in the research. Any remaining sera will be shipped back to Kenya.

Statistical analysis:

SAS software (SAS Institute, Cary, NC), and STATA software (STATA corporation, College Station, TX) will be used for quantitative data analysis. The primary analysis will be based on intention to treat. The analysis will be time to first clinical malaria comparing each of the study drug arms to the placebo arm. Mild, moderate, and severe anemia will also be compared between each study drug arm and the placebo arm.

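### The primary analysis is called intention to treat, yet the sample size section drops the expected 11% of allocated infants who have the outcome at an undefined baseline

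*Protocol*

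**What the plan says.** The Sample Size section plans on time to first clinical malaria episode and states: "We expect that 11% of infants will have the outcome measure at baseline and thus will be excluded from the primary analysis". It then inflates 250 per arm to 379 per arm (1516 in total) for this exclusion, 10% loss to follow-up and 13% mortality.

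The statistical analysis paragraph under Data Management states: "The primary analysis will be based on intention to treat". It continues: "The analysis will be time to first clinical malaria comparing each of the study drug arms to the placebo arm". It names no modified population and does not mention a baseline exclusion.

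Under Assignment to interventions: "All infants whose parents or guardians agree to participate in the study will be assigned to one of the 4 treatment groups". Malaria is not among the exclusion criteria. The section on infants who are febrile and parasitemic at enrollment ends: "These patients will be included in the study".

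The outcome itself is given under Definitions: "A clinical malaria episode in an infant will be defined as an axillary temperature of at least 37.5" degrees C, together with asexual *P. falciparum* parasitemia of any density.

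**The concern.** An intention-to-treat analysis keeps every randomised infant in the assigned arm. Removing about one infant in nine on a clinical finding is a different analysis set, and the protocol commits to both as primary.

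The exclusion also cannot be applied as written, because baseline is not tied to a visit:

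- Study Design and Sampling procedure recruit at the 6-week visit.
- The Iron section speaks of recruitment at 10 weeks.
- The Sample Size section counts its 68 weeks from the first intervention visit, which is at 10 weeks.

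An infant with an episode at 8 weeks, enrolled but not yet dosed, could be excluded, counted as an event or ignored. The Study Schedule lists no routine blood film at 6 or 10 weeks. Only infants with fever or a recent history of fever are tested then, whereas the outcome needs a measured temperature. Two analysts following this text could build different primary datasets.

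What is at stake is precision and the population to which the result applies. The excluded infants are enrolled, dosed and followed, and they can have a new episode. The protocol's Justification is to inform policy on an intervention delivered at routine immunization visits, and such visits would also reach infants with early malaria.

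**Working it through.** **Inputs, all from the Sample Size section unless marked**

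- 250 evaluable infants per arm; 379 per arm and 1516 in total after inflation.
- 11% with the outcome at baseline, 10% loss to follow-up, 13% mortality.
- "The sample size required for 90% power to detect a protective efficacy of 40"%, taken as a hazard ratio of 0.6.
- "Bonferroni adjustment 0.05/3 tests=0.017". Sidedness is not stated; two-sided is assumed.
- Placebo median of 68 weeks from the first intervention visit.
- Assumed: exponential times; follow-up of 42, 68 or 94 weeks (from 10 weeks of age to about 12, 18 and 24 months); the same hazard in infants with and without malaria at baseline.

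**1. Reproduce the plan's inflation**

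- Additive: 250/(1 − 0.11 − 0.10 − 0.13) = 250/0.66 = 378.8, so 379 per arm and 4 × 379 = 1516. This matches exactly.
- Multiplicative: 250/(0.89 × 0.90 × 0.87) = 358.7, so 359 per arm. This does not match.

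The 11% is therefore taken off the number allocated to each arm. It is not a screening loss. The infants affected are 0.11 × 379 = 41.7, about 42 per arm, and 0.11 × 1516 = 166.8, about 167 in all.

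**2. Reproduce the 250**

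- Schoenfeld events: 4 × (2.387 + 1.282)² / (ln 0.6)² = 206.3, so 207.
- Over 68 weeks, the event probability is 0.500 on placebo and 1 − exp(−0.6 × ln 2) = 0.340 on active drug, mean 0.420.
- Per arm: 207/(2 × 0.420) = 247 after rounding up (Freedman's formula: 216 events, 258 per arm).

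The stated 250 is consistent with about 68 weeks of follow-up.

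**3. Requirement without the exclusion**

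- 250/(1 − 0.10 − 0.13) = 250/0.77 = 324.7, so 325 per arm and 1300 in total. The 379 per arm covers it.

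**4. Power at 379 per arm, with and without the exclusion**

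Power = Φ(√d × |ln 0.6|/2 − 2.387), where d is the expected number of events in one active-versus-placebo comparison.

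*Losses and deaths (23%) removed outright.* Contributing infants: 379 × 0.66 = 250 per arm with the exclusion, 379 × 0.77 = 292 without.

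| Follow-up | With exclusion | Without | Gain |
| --- | --- | --- | --- |
| 42 weeks | 0.750 | 0.822 | 7.2 points |
| 68 weeks | 0.906 | 0.947 | 4.1 points |
| 94 weeks | 0.961 | 0.982 | 2.1 points |

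*Losses and deaths as censoring,* at hazard −ln(0.77)/42 = 0.00622 per week, with placebo event hazard ln 2/68 = 0.01019 per week. Analysed: 379 × 0.89 = 337 per arm with the exclusion, 379 without.

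| Follow-up | With exclusion | Without | Gain |
| --- | --- | --- | --- |
| 42 weeks | 172 events, 0.832 | 193 events, 0.878 | 4.6 points |
| 68 weeks | 236 events, 0.937 | 265 events, 0.962 | 2.5 points |

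The gain is about 2 to 7 points. Whether power lies above or below 90% is decided mostly by the follow-up length, which is a separate question.

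**The case against.** The strongest defence is that restricting a time-to-first-event analysis to infants free of the event at time zero is a recognised choice. No study drug is given before the 10-week visit and treatment is masked, so an exclusion made on a blinded pre-dose finding falls alike on all arms. On that view the fault is one of labelling: call the population modified intention to treat and define it. The point about validity stands, and so does the fact that the sample size was inflated to pay for the exclusion. But the protocol neither names such a population nor fixes the baseline visit, so the conflict remains, and the exclusion still gives up information that the trial collects anyway.

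Three stronger readings are tempting, and the document does not support them:

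- *That the exclusion biases the comparison.* Nothing shows this if the finding is made blind and before dosing.
- *That it takes the trial below its 90% target.* The 42-week figures fall below 90% with or without the exclusion. At 68 weeks, the duration that reproduces the 250, all the figures are above 90%.
- *That the enrollment section also contradicts the exclusion.* Its closing sentence says that febrile, parasitemic infants are enrolled. An infant can be in the study and outside one analysis set.

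The 11% is also a planning expectation. With testing triggered by fever, the number who meet the definition at a single visit is uncertain.

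**Conclusion.** The concern holds as a contradiction over the primary analysis population, joined to an undefined baseline. It should be corrected. It does not threaten the validity of the trial, provided that the condition is ascertained blind and before the first dose.

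The size is about 42 infants per arm (167 of 1516) left out of the primary analysis, at a cost of roughly 2 to 7 points of power with 379 per arm. That range rests on a two-sided alpha of 0.017, exponential times, an assumed follow-up of 42 to 94 weeks, two ways of handling the 23% lost or dead, and equal hazards in infants with and without baseline malaria. The contradiction and the 379 reconstruction need none of these assumptions.

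A reader might infer that allocation must move to the 10-week visit to cure this. It need not: a stated time origin and a common at-risk rule resolve the conflict within the present design.

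**What to change.** In the Sample Size section and the statistical analysis paragraph:

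1. Delete the exclusion from the primary analysis.
2. State that all randomised infants are analysed as assigned, for the first new clinical malaria episode counted from one time origin, the 10-week first-dose visit.
3. State when an infant with an episode at that visit becomes at risk of a new one, using a rule identical in all arms.
4. Keep the analysis without infants who have the outcome at baseline as a sensitivity analysis, with baseline defined by visit and by test.

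The minimum alternative is to name a modified intention-to-treat population, define its baseline, and withdraw the unqualified statement. That removes the contradiction but keeps the loss of information.

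The cost is wording only. No visits or infants are added, since 325 per arm would suffice on the plan's own inflation and 379 are planned. The downside is that the at-risk window for infants with malaria at baseline has to be fixed in advance.

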## Sampling procedure

All infants attending one of the study clinics for 6-week vaccination visit (the first post-birth scheduled EPI visit in Kenya) will be screened for enrollment. The parents or guardians of infants meeting the study inclusion criteria and not meeting any of the exclusion criteria will be offered enrollment in the study.

## Assignment to interventions

All infants whose parents or guardians agree to participate in the study will be assigned to one of the 4 treatment groups through permuted block randomization[50]. The randomization code will be prepared before the trial starts.

These randomization procedures are expected to minimize the possible influence of geographical location and seasonal malaria variations.

# Clinical Procedures

## Enrollment

At enrollment, capillary blood samples will be taken using finger or heel prick and collected into capillary tubes for later determination of antibodies to polio, diphtheria, tetanus, hepatitis B, and Hib.

It will take approximately 15 minutes for mothers of enrolled infants to respond to the enrollment questionnaire, which will be administered face to face by a trained interviewer, and for the capillary blood sample to be obtained.

The mother of each enrolled child will be issued an identity card with a photo of the infant and mother that will be used to confirm identity of the child at both scheduled and unscheduled visits for the duration of the study.

## Study drugs

As this is an efficacy study, all doses of antimalarials (or placebo) will be supervised. All enrolled infants will receive Day 1 dose(s) of study drugs during the 10 and 14 week intervention visits and again at the 9 month intervention visit. On days 2 and 3, parents will either be asked to return to the clinic for study drug administration, or the dose will be administered in the home by a compliance monitor. In the case of infants whose guardians were asked to return to clinic to receive the 2nd and 3rd doses of medication and who do not appear by noon of the appointed day, a compliance monitor will visit the home to administer the dose of medication. All medications will be dispensed as crushed tablets, not as commercial suspensions, in order to ensure accurate dosing. Mixing with syrup will be done at the moment of delivery to make the medicines more palatable.

*Sulfadoxine-pyrimethamine (SP) and artesunate*

SP (DAFRA Pharma, Belgium) will be given by the study team as crushed tablets suspended in syrup. The dose-equivalent will be one ½-strength tablet (250 mg sulfadoxine, 12.5 mg pyrimethamine) for all infants given a single time on the first day of treatment. The artesunate dose will be one 25 mg tablet, once daily for 3 days, also given as a crushed tablet in syrup.

*Chlorproguanil-dapsone (Lapdap)*

Lapdap (Glaxo-Smithkline, United Kingdom) will also be given as crushed tablets suspended in syrup. One pediatric LapDap caplet (15 mg chlorproguanil and 18.75 mg of dapsone) will be administered once daily for 3 days.

*Amodiaquine + artesunate* (DAFRA Pharma, Belgium)

Amodiaquine will be given as crushed tablets suspended in syrup. The dose will be one 67.5 mg tablet daily for 3 days. Artesunate will be given as for the SP arm.

*Placebos* (DAFRA Pharma, Belgium)

To ensure masking, placebo (tablets of lactose and maize starch) and treatments will be indistinguishable in terms of color and appearance, and will be provided pre-crushed in identical tubes that will be grouped as 6 tubes for each child. In the case of SP/AS3, the first day will have two tubes in the pack containing study drug (one containing SP and one containing AS), and the remaining days will have one tube with placebo (for SP) and one tube with AS. In the case of AQ, the first, third, and fifth tubes in the pack will contain AQ and the all other tubes will contain AS. In the case of Lapdap, the first, third, and fifth tubes will be study drug, and the other tubes will contain placebo. All tubes will contain placebo for the placebo arm.

### Iron

Twelve mg/day of oral iron (roughly 2 mg/kg/day) will be given to all study children for 4 months (from recruitment at 10 weeks until 6 ½ months of age). Iron will be given as drops of a concentrated solution of ferrous sulfate containing 25 mg/ml. A one month supply will be given at the 10-week visit, an additional one month supply will be given at the 14-week visit, and a 2 month supply will be given at the 18 week visit. Iron will be dispensed in bottles with a dropper device in the neck to facilitate accurate dispensing and with a childproof closure. Compliance with iron therapy will be assessed by using a measuring stand to determine quantity used at the 14 week, 18 week, and 6 ½ month study follow-up visits ([name], personal communication).

### Drug quality

We will obtain the manufacturer’s certificate of analysis for one lot of each study drug.

## Children who are febrile and parasitemic at enrollment

Infants who have documented fever (> 37.5 C by axillary measurement) or history of recent fever (in the previous 48 hours) will have a rapid diagnostic test (RDT) for malaria performed. If the RDT is positive, the infant will be given antimalarial treatment in accordance with national policy. A blood film will also be performed; febrile infants who had a negative RDT, but on later blood film examination have parasitemia will be given antimalarial treatment in accordance with national policy. These results and the antimalarial therapy will be delivered to the infant’s home only if the results of the blood film are positive while the RDT was negative. These patients will be included in the study.

## Intervention clinic visits

Enrolled infants returning to clinic at 10 weeks will be given study drugs and will be measured for recumbent length, weight, and mid-arm upper arm circumference. Capillary blood samples will be taken using finger or heel prick for later G6PD enzyme level testing. Blood will be collected on filter paper at the 10 week visit for later testing for genetic markers for drug resistance. Infants returning to the clinic at14 weeks will be given the 2nd dose of the study drugs. At the 9-month visit, infants will be given the final dose of the study drugs and a capillary blood sample will be taken for later measles serology testing.

A questionnaire soliciting information about overall health of the baby, febrile episodes, other intercurrent illnesses, use of other medications, ITN usage, and compliance with iron will be administered at each clinic visit. The form will be based on the OPD surveillance form used in the DSS, but will solicit more detailed information. Infants whose caretakers state that their child has been given CTX in the past 2 weeks will either a.) not be given the dose of intervention drug until 2 weeks after CTX was given, or b.) be withdrawn from the study (if CTX is given as a daily dose).

If the infant is reported or observed to be ill, a full clinical exam will be performed. Infants at the 10- and 14-week visits who have documented fever (> 37.5 C by axillary measurement) or history of recent fever (previous 48 hours) will have an RDT for malaria performed. If the RDT is positive, in order to maintain blinding of the study groups, there will be a treatment regimen paired to each of the study arms. In the case of the three arms that include an antimalarial (SP/AS, AQ/AS and Lapdap), the “treatment” drug will in fact be a placebo. Each of the three non-placebo arms of the study involves the administration of a drug that is adequate and appropriate treatment for malaria. In the case of children enrolled in the placebo arm of the trial, the treatment drug will be a 7-day course of quinine, which is one of the MOH recommended drugs for treatment of malaria. The guardians of all febrile children will also be provided with a 3-day supply of acetaminophen (paracetomol). A blood film will also be performed on all infants who have an RDT performed. Any infant who was febrile, but had a negative RDT and is found to have parasitemia by blood film will be given antimalarial treatment in accordance with the paired scheme above. Infants who appear pale will have their hemoglobin measured. Infants with Hb<8 g/dl at the 9 month visit (as infants at the 10 and 14-week visits will already be taking iron) will receive iron per the national policy.

At each of the study clinics, compliance monitors will work in conjunction with a village recorder to remind enrolled families (with an oral and written message delivered to the home) about upcoming study clinic visits. A compliance monitor will visit the houses of families who fail to appear within one week of an intervention visit (10 weeks, 14 weeks, and 9 months).

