## Follow-up clinic visits (non study drug administration visits)

Parents will be asked to bring enrolled infants back to the clinic for follow up visits at 18 weeks, and at 12, 18, and 24 months. A compliance monitor will visit the houses of families who fail to appear within 2 weeks of a follow-up visit. To facilitate the work of compliance monitors, a photograph of each mother and child will be made at enrolment, and that photograph kept with a map locating the place of residence. These documents will be returned to the mother at the conclusion of the study or destroyed.

At the 18-week visit, blood (from the same finger prick) will be obtained and frozen at –70C for later determination of post-vaccination serologic testing for antibodies to polio, diphtheria, tetanus, hepatitis B, and Hib. At the 12-month visit, blood will be obtained for determination of sickle cell trait and frozen for later determination of measles antibody titer. Blood will also be collected on filter paper for later testing of genetic markers for drug resistance.

A questionnaire (identical to that administered during the intervention visits) soliciting information about overall health of the baby, febrile episodes, other intercurrent illnesses, use of other medications, ITN usage, and compliance with iron will be administered.

The algorithm for antimalarial treatment of children who are febrile at the 18 week, and at 12, 18, and 24 month visits will be the same as for the intervention visits, with the exception that all infants who need treatment will be provided quinine (18-week visit) or Coartem (12, 18, and 24-month visit if the child weighs at least 5 kg), as no children will be receiving study drugs at these visits. Children weighing less than 5 kg requiring antimalarial treatment will receive quinine. Children with severe malaria will treated with quinine, regardless of age. Infants with Hb<8 g/dl at the 12, 18, or 24-month visits will be treated with iron per the national policy.

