## Unscheduled visits

Parents of enrolled infants will be instructed to take them to one of the study health facilities for evaluation and treatment of all illnesses. Study infants who make such unscheduled visits for febrile illness during the study period will have a malaria RDT performed. Those with a positive RDT will be treated with a treatment course of quinine if they present before their 12-month visit. Treatment with quinine (instead of SP or Coartem) will avoid the possibility of giving doses of SP or artemisinin that are too closely spaced in time while the child is receiving study drugs. Those with a positive RDT at or after their 12-month visit will receive Coartem, unless they weigh less than 5 kg, in which case, they will receive quinine. All children who are febrile will also have a malaria blood film performed at the same time. All children who have a blood sample taken for malaria diagnosis or have signs or anemia will also have a hemoglobin measurement performed. If any infant who had documented fever but was negative for malaria by RDT is later found to have malaria by microscopy, the results and a treatment course of quinine (or Coartem) will be delivered to the infant's home. Blood from the same finger-stick blood sample will be dried on to filter paper for analysis on molecular markers of antimalarial drug resistance.

During weekends and evenings, a nurse will be available to assist IPTi participants who are severely ill. The nurse will be stationed at Lwak hospital, our most central study clinic. In cases where the infant must be hospitalized, the nurse will provide stabilizing treatment and the IPTi Field Supervisor, Coordinator, or designee will arrange transport to Bondo or Provincial hospital.

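### Active-arm infants whose study dose is deferred for recent cotrimoxazole would receive only placebo for confirmed malaria at the 10- or 14-week visit

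*Protocol*

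**What the plan says.** Two rules stand next to each other in the Protocol, Intervention clinic visits.

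- **Cotrimoxazole (CTX) rule.** An infant reported to have had CTX in the past 2 weeks will "not be given the dose of intervention drug until 2 weeks after CTX was given". Withdrawal is reserved for infants on daily CTX. An infant given a short course therefore stays in the trial, and the dose is postponed.
- **Treatment rule.** "Infants at the 10- and 14-week visits who have documented fever", or a history of fever in the previous 48 hours, have a rapid diagnostic test (RDT). If it is positive, the treatment is paired to the randomised arm. In the SP/AS3, AQ/AS3 and Lapdap arms the treatment "drug will in fact be a placebo"; in the placebo arm it is a 7-day course of quinine. A febrile infant with a negative RDT and a positive film "will be given antimalarial treatment in accordance with the paired scheme above".

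The reason given for placebo treatment is this: "Each of the three non-placebo arms of the study involves the administration of a drug that is adequate and appropriate treatment for malaria".

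Elsewhere the Protocol uses real treatment whenever no study drug is being given. Under Follow-up clinic visits, all infants needing treatment get quinine or Coartem, "as no children will be receiving study drugs at these visits". Under Unscheduled visits, "Those with a positive RDT will be treated with a treatment course of quinine if they present before their 12-month visit", whatever the arm. At enrollment, infants with a positive test are treated by national policy.

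**The concern.** The paired treatment is chosen by randomised arm, not by whether a dose was given that day. Its safety rests wholly on the study drug serving as the treatment. When the dose is deferred, that support is gone, but the pairing still applies.

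An active-arm infant with fever, a positive test and a short CTX course in the past 2 weeks would then leave the clinic with placebo and paracetamol. A placebo-arm infant in the same position would leave with quinine. The harm is untreated, test-confirmed malaria at about 10 to 14 weeks of age, at a site where the Protocol reports infant mortality of 176 per 1,000 live births and attributes about 20% of infant deaths to malaria.

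The clinician cannot correct this at the visit. Because of the blind, nobody there knows whether the paired pack holds quinine or placebo.

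**Working it through.** **Reading the rules together**

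| Situation | Study drug given? | Treatment, active arms | Treatment, placebo arm |
|---|---|---|---|
| Enrollment, 6 weeks | No | National policy drug | National policy drug |
| 10 or 14 weeks, dose given | Yes | Placebo (study drug is the treatment) | Quinine |
| **10 or 14 weeks, dose deferred for CTX** | **No** | **Placebo** | **Quinine** |
| Follow-up visit | No | Quinine or Coartem | Quinine or Coartem |
| Unscheduled, before 12-month visit | No | Quinine | Quinine |

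Only the third row leaves an infant with confirmed malaria without an antimalarial. The exception for follow-up visits names the 18-week and the 12-, 18- and 24-month visits and no others. The sentence on quinine for severe malaria stands in the follow-up section; even if read generally, it leaves uncomplicated malaria uncovered. The exclusion criteria bar only current CTX prophylaxis, so infants who later receive a short course can be in the trial.

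**Length of the gap.** It ends when the deferred dose is given, 2 weeks after CTX. That is at most about 14 days, and less if CTX was given some days before the visit.

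**Number of infants.** The Protocol gives no rate of CTX use, so only an illustration is possible.

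Inputs:
- Sample size 1,516, with three of four arms active: 1,516 × 3/4 = 1,137 infants.
- Malaria at the 10-week visit: assumed equal to the 11% with the outcome at baseline (Sample Size). That section places the 18-month median 68 weeks after the first intervention visit, and 10 + 68 = 78 weeks, about 18 months. Baseline at 10 weeks is therefore a reasonable reading.
- Malaria at the 14-week visit: assumed to be at most the placebo risk over 4 weeks with an exponential median of 68 weeks, 1 − exp(−ln 2 × 4/68) = 0.040.
- Attendance: full, or the 79.4% and 66% coverage of the second and third DPT doses (Study site).
- Recent CTX use is taken as independent of malaria. The range of 1% to 10% for CTX use is an assumption without a source in the Protocol.

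Per 1% of infants with CTX in the prior 2 weeks:
- Full attendance: 1,137 × 0.11 × 0.01 = 1.25 at 10 weeks, plus 1,137 × 0.040 × 0.01 = 0.45 at 14 weeks; total 1.7.
- Coverage as cited: 1,137 × 0.794 × 0.11 × 0.01 = 0.99, plus 1,137 × 0.66 × 0.040 × 0.01 = 0.30; total 1.3.

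For CTX use of 1% to 10%: from 1.3 × 1 = 1.3 up to 1.7 × 10 = 17 infants.

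Sensitivity: if the 11% belongs to the 6-week enrollment visit instead, and 4.0% is used at both visits, the figures per 1% fall to 1,137 × 0.040 × 0.01 × 2 = 0.9 (full attendance) and 1,137 × (0.794 + 0.66) × 0.040 × 0.01 = 0.66 (coverage as cited). The range for 1% to 10% is then about 0.7 to 9.

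**Effect on the primary endpoint.** Infants with measured fever and parasitemia at the visit have either already had the event (Definitions) or are excluded at baseline (Sample Size). Little is left to bias time to first clinical malaria.

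**The case against.** The strongest reply is that this is an unforeseen edge case and not an instruction to withhold treatment. The pairing is explained by the dosing of the active arms, and the follow-up section states the converse, so a reader guided by purpose would give quinine when no dose is given. The case also needs four things at once: recent non-daily CTX, fever, a positive test and an active arm. Families are told to attend for any illness, care is free, and an unscheduled visit with a positive RDT brings quinine in every arm. The count rests on assumed inputs.

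Much of this is fair on frequency. Few infants are likely to be affected, and the upper figure of 17 should carry little weight. It does not remove the fault. The pairing is worded by arm, and blinded staff can only follow the wording. The return visit depends on a family that has just been handed an apparent treatment and 3 days of paracetamol, which may delay it.

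**Conclusion.** The concern holds. For a 10- or 14-week visit at which the dose is deferred for CTX, the written rules give placebo for confirmed malaria in three of the four arms, against the Protocol's own principle for visits without study drug. The gap lasts at most about 14 days and closes sooner if the infant returns unscheduled and is RDT-positive. Roughly 1 to 17 infants over both visits would be affected if 1% to 10% had recent CTX; about half that if the 11% baseline figure does not describe the 10-week visit. The true number is unknown and probably small.

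It should be corrected nonetheless, because the harm to each affected infant is serious, foreseeable and cheap to avoid. The case rests on patient safety and not on the analysis.

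**What to change.** Add to the treatment rule in Intervention clinic visits that the arm-paired scheme applies only when study drug is actually given at that visit. When the dose is deferred for CTX, every infant with a positive RDT or film, in all four arms, receives the same active antimalarial chosen by the investigators. Quinine is the natural choice, as it is already used at the 18-week and unscheduled visits. The investigators should also say whether a deferred dose that falls due during a 7-day quinine course waits until the course ends.

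The first part of the rule also stops the pairing for infants taken off study drug after an allergic reaction but still followed. Their code is already broken, and the Protocol already requires a drug from another class.

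The blind is kept: deferral is known at the visit without the code, and all arms are then treated alike. The cost is a sentence or two in the Protocol, one line in the clinic algorithm and some quinine already stocked, with no added visits or infants.
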